**Methods**

*Overview*

The overall purpose of this project is to (1) estimate the changes in taxed and untaxed beverage consumption that follow a novel SSB tax implementation; (2) examine SSB knowledge, SSB risk perception, and tax awareness are potential modifiers of the relationship between SSB taxes and SSB consumption; and (3) quantitatively examine the media response to the South African SSB tax. There is a strong empirical basis for conducting this study due to the evidence that SSB taxes have significant effects on SSB consumption^6,7,19,45^, that low knowledge about the health harms of SSBs is associated with increased SSB intake among adults^9^, and that public acceptance of policies are shaped by media framings^53,56,68,69^ and awareness^50^ of the policies. This study is premised upon the conceptual model presented in Figure 4, which shows how the effect of SSB taxes on SSB consumption may be modified by consumers’ knowledge about SSBs and understanding of their relationship with health outcomes as well as awareness of the SSB tax. Additionally, the discussion surrounding new SSB tax implementation generates a media response, the effect of which is partially mediated through changes in consumer knowledge and attitudes as well as other possible mechanisms whereby public discussion of taxes may affect SSB consumption. Thus, both baseline consumer knowledge as well as media influences on consumer knowledge affect SSB consumption. We proceed to outline the approach for each of our aims below.

**
[figure not shown]
**

**Figure 4.** Conceptual Model of the relationship between SSB tax policy, its effect on the media, and the downstream effects on consumer knowledge and tax awareness. These variables are theorized to modify the effect of the relationship between time since taxation and SSB consumption.

*Key databases*

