After the confirmatory factor analysis, we will first test whether our potential modifiers change significantly over time. This will be done by setting our latent variable—for SSB knowledge and then for risk perception—as a continuous dependent variable in a linear regression model and entering time (coded 0, 1, 2 for baseline, 6 and 12 months, respectively) as the independent variable. The coefficient for time will indicate the change in knowledge (or risk perception) for a unit change in time period, and the p value will indicate whether this result is statistically significant. For the binary variable tax awareness (yes/no), we will measure change over time using two sample t-tests, comparing the mean awareness at 6 months to baseline and 12 months to baseline.

Next, we will determine whether SSB knowledge, SSB risk perception, or tax awareness modify the relationship between time and taxed beverage consumption. Using linear regression models, we will test whether the relationship between our potential modifiers and taxed SSB consumption differs by time using interaction terms. We will test for interaction with a Wald test. We will conduct a pooled analysis using all observations from baseline, 6 months, and 12 months post-tax when testing these models, with dummy variables coded 0, 1, 2 to indicate each data collection time period. Our potential modifiers of SSB knowledge and risk perception will be kept as continuous variables because categorization results in a loss of information, and there is no substantive reason for creating arbitrary cutoffs when testing this interaction. Models will be controlled for individual level covariates listed in Table 4, weekday of interview, and temperature (to control for seasonality).

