**Expected Results:** In accordance with our conceptual model, we expect to see tax awareness, SSB knowledge, and SSB risk perception to increase over time. We expect a significant interaction between time of data collection and SSB knowledge score, such that a higher knowledge about health risks will be associated with lower SSB intake, and this relationship will be stronger after the tax. This would suggest that knowledge is a statistically significant modifier of the change in SSB consumption after the tax in our sample. We expect to see similar effect modification for risk perception. For tax awareness, we expect there to be a statistically significant increase at 12 months given that participants will have noticed increased prices of SSBs in shops. We expect a significantly lower taxed beverage intake among those who are aware of the SSB tax at 12 months compared to those who are unaware. It is possible that there is no difference in awareness at 12 months after the tax compared to baseline, recorded the month before the tax was implemented. This result would suggest that media coverage of the tax has not penetrated into the Langa township, and will provide some explanation for the possibility of finding a small amount of change in Aim 1.

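### Aim 2's time-by-modifier test can reject with an identical tax response in everyone, if the newly aware or knowledgeable differ in usual intake from those already so

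*Protocol*

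**What the plan says.** The analysis is set out in the Protocol under Aim 2, in the text that follows the confirmatory factor analysis. Data from baseline, 6 and 12 months are pooled, and "we will test whether the relationship between our potential modifiers and taxed SSB consumption differs by time using interaction terms", using a Wald test. Each modifier is the value recorded in the same survey wave as intake.

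The Expected Results of Aim 2 then say three things that matter here.
- The modifiers should move: "we expect to see tax awareness, SSB knowledge, and SSB risk perception to increase over time".
- For awareness, the reason is the tax itself: "we expect there to be a statistically significant increase at 12 months given that participants will have noticed increased prices of SSBs in shops".
- A significant interaction with knowledge is read as follows: "This would suggest that knowledge is a statistically significant modifier of the change in SSB consumption after the tax in our sample". Similar modification is expected for risk perception. For awareness the expectation is put differently, as a contrast with people who do not know of the tax: "We expect a significantly lower taxed beverage intake among those who are aware of the SSB tax at 12 months compared to those who are" […].

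The Methods overview places knowledge and attitudes downstream of the tax. The tax generates a media response, "the effect of which is partially mediated through changes in consumer knowledge and attitudes". The Aim 1 limitations state that participants' identifiers do not allow anyone to be followed from one wave to another.

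**The concern.** Effect modification asks whether people who differ in knowledge or awareness respond differently to the tax. That needs groups whose membership the tax does not alter, or a way to carry a pre-tax value forward. This design has neither. The aware at baseline and the aware at 12 months may be different kinds of people, and the protocol's own model gives a reason to expect so.

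A changed slope between waves can then mean that the knowledgeable responded more, or that people with different usual intake became knowledgeable. The planned test cannot separate the two, and the Expected Results name only the first.

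The protocol intends identified modifiers to guide the targeting of future policy (Significance, section on behaviour change). A composition effect could therefore be taken as a policy lever, or could hide a real one.

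**Working it through.** **No figure to reproduce.** The protocol gives no power, alpha or effect size for the Aim 2 interaction. The sample size under Study Power concerns the Aim 1 change in mean intake and is not used here.

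**What the interaction estimates.** Take awareness, with two waves. Let U be usual intake and let everyone's intake fall by the same amount d. The aware-minus-unaware gap is G0 at baseline and G12 at 12 months.

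- G0 = E(U | aware at 0) − E(U | unaware at 0)
- G12 = [E(U | aware at 12) − d] − [E(U | unaware at 12) − d]
- Interaction = G12 − G0. The response d cancels.

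With identical response, the interaction is only the change in how usual intake differs between aware and unaware people. It is zero if that relation is stable, and non-zero otherwise.

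**Inputs to the simulation.**
- From the protocol: 2,383 participants (the baseline number; the later waves are assumed equal); total SSB intake of mean 1054 ml and SD 1071 ml (Table 1); a 6% fall, given to everyone.
- Assumed, because the protocol gives no value: 30% aware at baseline, unrelated to intake; on average half of the rest become aware, so 0.30 + 0.70 × 0.50 = 0.65; lognormal intake with half the log-variance due to usual intake; a range of odds ratios for becoming aware per SD of usual intake.
- Alpha: 0.10 is stated only for study power, so 0.05 is shown as well.
- Test statistic: z = (G12 − G0) / sqrt(var G0 + var G12).

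**Results with zero true modification.** Ranges cover repeated independent runs.

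| Odds ratio of becoming aware | Mean interaction (ml) | Rejects at 0.10 | Rejects at 0.05 | Rejects at 0.10 in the hypothesised (negative) direction |
|---|---|---|---|---|
| 1.00 | about 0 | 10–12% | 4–5% | 5% |
| 1.25 | +97 | 46–47% | 35–36% | 0.1% |
| 1.50 | +177 | 86–87% | 79% | 0% |
| 0.80 | −99 | 45–47% | 34% | 45% |
| 0.67 | −177 | 85–88% | 79% | 88% |

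**Three waves, 2-df Wald test at 0.05, SD 603 (Study Power) or 1071 (Table 1).**
- Share aware constant at 30%: 4–7%.
- Newly aware drawn at random, but the early-aware drink 200 ml less; awareness 30/40/50%: 47% (SD 603) or 19% (SD 1071). New entrants dilute the gap, so the interaction is positive.
- Lighter consumers more likely to become aware (correlation 0.1), same awareness path: 29% or 27%, negative.
- Awareness rising from 30 to 50% with a constant underlying correlation with intake of 0.2: 5–7%.
- Knowledge rising uniformly: 4–6%. Gains random, or larger in the less informed, with a baseline slope of −50 ml per SD: 8–12%. Gains larger in lighter consumers: 99–100%.

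**The awareness comparison at 12 months only.** Suppose aware people already drank 10% less before the tax, half are aware, and there is no modification.
- Difference: 0.10 × 1054 = 105.4 ml
- Standard error: 1071 × sqrt(2 / 1191.5) = 43.9 ml
- z: 105.4 / 43.9 = 2.40
- Chance of a significantly lower result: Φ(2.40 − 1.96) = 67% at 0.05; Φ(2.40 − 1.645) = 78% at 0.10

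A single-wave gap therefore says little about the response to the tax.

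**The case against.** The protocol is not silent. The Aim 2 limitations disclaim causal conclusions, say that different sets of people are compared, and admit that true modification is hard to tell from social desirability bias. The methods text already describes the test as a difference in association over time, and the Expected Results are hedged. All of this stands. But social desirability is a reporting bias; no caveat mentions that membership of the aware or knowledgeable group may itself change, and the interpretive sentence remains.

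Three stronger readings are tempting and are not supported.

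- *Any rise in awareness or knowledge makes the test reject.* It does not. A uniform rise in knowledge, or awareness unrelated to intake, leaves the test near its nominal level. The modifier's relation to usual intake has to change.
- *People noticing prices would falsely confirm the hypothesis.* The protocol expects awareness to rise "given that participants will have noticed increased prices of SSBs in shops", and a reader may infer that heavy buyers notice most; the protocol does not say so. If they did, the false interaction would be positive, against the hypothesis. False confirmation needs lighter consumers to become aware or knowledgeable.
- *The plan tests modification by awareness at 12 months alone.* It does not. The one-wave comparison is an expected result, and the planned model contains the proper contrast.

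The sizes also rest on assumed awareness levels and selection strengths. The SD is for total SSBs by frequency questionnaire, whereas the main outcome is the 24-hour recall and Aim 2 concerns taxed beverages. The Table 4 covariates were not simulated. The headline figures concern awareness; those for knowledge range from nominal to near certainty, depending on who gains.

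**Conclusion.** The concern holds in conditional form. The modifiers are measured after exposure, in unlinked samples, and the protocol expects the tax to move them. A significant interaction cannot by itself be read as modification of the response to the tax.

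Under the stated assumptions, with no true modification, rejection at alpha 0.10 is about 46% at an odds ratio of 1.25 or 0.8 per SD of usual intake and about 87% at 1.5 or 0.67, against about 11% without selection. The error can run either way: masking modification if heavier consumers become aware, mimicking it if lighter consumers do. The percentages illustrate sensitivity and do not forecast what this survey will show. That the interaction mixes composition with response needs none of the assumed values.

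**What to change.** In the Aim 2 Expected Results, replace the interpretive sentence on knowledge with: *the cross-sectional association between knowledge and intake differs between waves, which may reflect a change in who is knowledgeable as well as a different response to the tax.* Use the same wording for risk perception and awareness.

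Base the awareness conclusion on the aware-unaware difference at 12 months minus that at baseline. This is already a term in the planned interaction model. It removes a stable pre-tax gap, but not the effect of changing membership, so the revised wording is needed for it too.

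A sensitivity analysis using modifiers predicted from age, sex and living standards is not recommended: it would test whether the change in intake differs by those characteristics, not by knowledge or awareness.

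The cost is a few sentences and a weaker claim. No new data or models are needed.

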**Limitations**

We are limited in our ability to make causal conclusions from the analyses presented in Aim 2. One of the limitations on causal inference is that we are not able to track individuals over time, so we are restricted to estimating means of two different populations (time 1 versus time 2), rather than to examine changes in the same population of individuals over time. However, there is also an advantage of our cross-sectional study design compared to a longitudinal design for this analysis. Because we have a new set of individuals at subsequent time points, our study design will avoid the bias associated with repeating the same study questionnaire multiple times, which we would expect to be biased towards improved responses over time, after individuals understand the full set of questions to be asked including the negative health implications of high SSB consumption. It is also difficult for us to distinguish whether our results are indicative of true effect modification or whether they are due to social desirability bias. For example, if greater knowledge of the tax increases the likelihood of social desirability bias (i.e. recognizing that drinking SSBs is considered an unhealthy behavior), then those who increase in knowledge may underreport their actual taxed beverage intakes.

**Aim 3: Examine framing of newsprint articles related to the South African SSB tax, whether framing changes over time, and whether framing is associated with proposed causes and solutions for excessive SSB intake.** Beyond their potential impacts on public health, SSB taxes are subject to policy and ethical arguments both in academia^31,92–97^ and in the media^53,62,98^. Media representations of public health policies have a strong effect on public opinion and therefore can affect the likelihood of success or failure of policy proposals^33,55,69^. Media coverage may also increase public awareness of the tax, as we are testing in Aim 2. In this study, we will analyze the response to the SSB tax before and after its implementation in April 2018 to inform SSB policy advocacy in South Africa and across the region. We will perform a quantitative media content analysis of the twenty most widely read English-language online newspapers^99^ across multiple news genres in South Africa for six months preceding and following the SSB tax implementation. We will examine the media response to the tax by coding articles according to the affective attributes (positive, negative, or neutral) and the substantive attributes such as framing of the relationship between SSBs and health outcomes, assignment of responsibility (i.e. individual or industry), and proposed solutions (individual behavior or policy)^100^. We will also examine whether those articles that characterize the problem with excess sugary beverage consumption and weight gain as an individual problem are more likely to propose individualized solutions rather than public health policy solutions.

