After completion of the dietary intake assessment, participants completed a **knowledge and attitudes questionnaire**. This survey asked whether the participant could classify the beverage categories listed in Table 3 as either SSBs or non-SSBs as a demonstration of their knowledge of beverages containing added sugar (hereafter referred to as “knowledge”). Participant knowledge about SSBs was measured using a 1-3 scale for each beverage category listed in Table 3. Participants were asked whether each beverage category was (1) not sugary, (2) somewhat sugary, (3) sugary, or (4) do not know to determine the ability to identify SSBs among beverage categories. Next, after participants were given a definition of SSBs, they were asked to what degree SSB consumption increases the risk of a number of chronic diseases and risk factors including diabetes, high blood pressure, obesity, dental problems, and cancer (hereafter referred to as “risk perceptions”). The degree to which SSBs increased the risk of these conditions could be answered as (1) Not at all, (2) A little, (3) Somewhat, (4) A lot, or (5) Not sure. To assess perception of the tax, participants were asked (1) whether they were aware of the SSB tax (yes/no) and (2) whether they supported the taxation of unhealthy foods and beverages, answerable with strongly oppose, oppose, agree, or strongly agree. Finally, participants were asked whether they intended to reduce their consumption of any of the categories in Table 3 or their SSB consumption overall (“intentions”). Only one diet assessment and one knowledge questionnaire were completed for a single individual within a given household. If there was more than one person in the household, then the older individual (usually mother or grandmother) completed the household level questions. There were no households within which multiple individuals completed these assessments. At both 6 and 12 month data collection periods, participants were asked whether they had been previously surveyed, and if so, at which time period.

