**Limitations**

*Study design*

Given that our data are cross-sectional and not longitudinal, we are not able to follow individuals over time, only measure differences in population means. Social desirability bias could affect reporting of SSB intake and cause us to underestimate SSB intake. It is also possible that after the tax, social norms may have shifted so that the effect of social desirability bias is even greater after SSBs are subject to tax, causing an overestimation of reductions in SSB intake in this population.

*Repeated individuals across data collection periods*

We are using a repeated cross-sectional study design, and it is possible that we have repeated individuals surveyed at more than one time point. We do have a variable that indicates whether participants were included in our sample at previous data collection points, but the individual identifiers were generated using a method that does not allow for individuals to be linked across time. This limitation could potentially bias our results by an unknown magnitude and direction, given that we cannot know whether repeated individuals were high or low consumers of a given beverage category.

*Accuracy of FCT beverage codes*

Although the beverage codes that we are developing for our UNC-UWC FCT are based on nutrition information of South African beverages, they still represent an average and therefore it is possible that some beverages may be misclassified as taxed or untaxed if the actual products consumed differ in their sugar content to the average sugar content calculated for the beverage category. For example, if there is brand-specific reformulation, where some soda brands reduce their sugar (to become untaxed) and others do not (remain taxed), this could lead to misclassification. The potential for misclassification of beverages is even greater for the FFQ versus the 24-h recall because the beverage categories reported are broader than the individual beverage codes contained within each beverage subcategory.

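### Aim 2 says each wave is a new set of people and so escapes repeat-questionnaire bias, but Aim 1 says the same population may include repeats, and no stated analysis uses the previously-surveyed variable

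*Protocol*

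**What the plan says.** The protocol addresses repeat participation in three places.

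- **Aim 2, Limitations.** Presented as an advantage over a longitudinal design: "Because we have a new set of individuals at subsequent time points, our study design will avoid the bias associated with repeating" the questionnaire. The bias is described as one "which we would expect to be biased towards improved responses over time".
- **Aim 1, Limitations, on repeated individuals.** Here "it is possible that we have repeated individuals surveyed at more than one time point". The section notes that the data set records earlier participation. It rules out linkage, however: "individual identifiers were generated using a method that does not allow for individuals to be linked across time". The resulting bias is called unknown in both size and direction.
- **Measures and Data Collection.** At the 6- and 12-month rounds, "participants were asked whether they had been previously surveyed, and if so, at which time period".

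The Aim 2 introduction says that it uses the Aim 1 study population. The Aim 2 analysis text tests change in the two latent scores by "entering time (coded 0, 1, 2 for baseline, 6 and 12 months, respectively) as the independent variable". It tests awareness with two-sample t-tests against baseline, and effect modification in a pooled model adjusted for the Table 4 covariates, weekday and temperature. Table 4 does not list prior participation, and the Aim 1 regression models do not include it.

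**The concern.** One section claims as a strength a protection that another section says the design may lack. This matters because of the direction of the bias. Nobody can be a repeat respondent at baseline, so any carry-over falls entirely in the post-tax waves and is aligned with the time effect. Under Expected Results, Aim 2 predicts that awareness, knowledge and risk perception will rise, which is what learning from an earlier interview would also produce.

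The questionnaire makes carry-over plausible. A first-time respondent classifies drinks before hearing the definition of an SSB, whereas a repeat respondent has already heard it. Asking whether someone knows of the tax also tells them that it exists. Yet the protocol reads a rise in awareness as a response to shop prices, and no rise as a sign that media coverage did not reach Langa. A reader who accepts the Aim 2 statement would not think to discount any of this.

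**Working it through.** There is no figure in the protocol to reproduce. The check is mainly one of consistency, followed by an illustration of scale.

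**Consistency**

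1. Same population? Yes, according to the Aim 2 introduction.
2. Are earlier participants excluded? Nothing says so. Age is the only eligibility criterion given. The recruitment detail describes baseline, and follow-up recruitment is not separately described.
3. Were repeats foreseen? Yes. Prior participation and its wave were asked about, and Aim 1 lists repeats as a limitation.
4. Is the variable used? Not in Table 4, the Aim 1 models, or the Aim 2 change and interaction models.
5. Does the lack of linkage prevent its use? It rules out paired or clustered modelling. It does not rule out counting repeats by wave or restricting an analysis to first-time respondents.

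**Scale (illustration only)**

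Inputs from the protocol: 2,383 households at baseline; 17,402 households and 52,401 inhabitants in Langa; one respondent per household for the diet and knowledge instruments. Assumptions: each wave is an independent random draw of 2,383 households, and repeats score higher by a learning effect of 0.1 or 0.2 SD. The protocol gives neither follow-up sample sizes nor a learning effect.

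- Household overlap with one earlier wave: 2,383/17,402 = 13.7%.
- Household overlap with either of two earlier waves: 1 − (1 − 0.137)² = 25.5%.
- Inhabitants per household: 52,401/17,402 = 3.0. A repeat household need not yield a repeat respondent. If the respondent were picked at random from k eligible members, overlap with one wave would be 13.7%/k: 6.8% for k = 2 and 4.6% for k = 3. At 12 months, 1 − (1 − 0.137/k)² gives 13.2% and 8.9%.
- Standard error of a difference between two wave means, in SD units: √(2/2,383) = 0.029.
- Shift in a wave mean = repeat share × learning effect. At 12 months with 0.2 SD, the shift is 0.051 SD (z = 1.76) for k = 1, 0.026 SD (z = 0.91) for k = 2 and 0.018 SD (z = 0.62) for k = 3.

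Chance of a two-sided p < 0.05 when nothing has truly changed, from Φ(z − 1.96) + Φ(−z − 1.96), against a nominal 5%:

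| Share of repeats | 0.1 SD | 0.2 SD |
|---|---|---|
| 13.7% | 8% | 16% |
| 25% | 14% | 41% |
| 50% | 41% | 93% |

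These figures are for a contrast of two wave means, not for the linear time term in the plan. The 50% row is hypothetical: it would need repeated visits to the same doors, which the protocol neither states nor excludes.

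**The case against.** The strongest reply is that the risk is already disclosed. Aim 1 names repeated individuals openly, and the Aim 2 sentence compares the design with a cohort in which everyone repeats, against which partial repetition does carry less of this bias. On this view one sentence is worded too strongly. A statistical analysis plan that is not shown may also use the variable. The first part stands as far as it goes: the bias may well be smaller than in a cohort. But smaller is not avoided, and an analysis plan would not make the protocol's two statements agree.

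A reader might also infer more than the documents support:

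- **That a quarter of the 12-month respondents had been interviewed before.** The 25.5% is a household figure under an assumed random draw, and it overstates the overlap of individuals under that same assumption.
- **That learning would produce the hypothesised Aim 2 interaction.** A uniform rise in knowledge does not by itself create a time-by-knowledge interaction on intake. That needs reporting of intake to depend on knowledge, and the Aim 2 limitations already raise under-reporting of that kind.
- **That the Aim 1 reduction is inflated.** This is possible, but nothing in the protocol gives its size.
- **That comparing previously surveyed with first-time respondents within a wave would reveal the bias.** The two groups may differ in residential stability, being at home and willingness, so the gap mixes selection with learning. Prior participation is also self-reported.
- **That first-time respondents should be the main analysis set.** Baseline includes easily reached people who would then be removed at follow-up, so the contrast could compare differently selected groups.

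**Conclusion.** The contradiction is real. The Aim 2 claim that repeat-questionnaire bias is avoided is not supported by the protocol's own account of its sample, and the variable that would show the extent of repetition enters no stated analysis. By the protocol's own description the bias runs towards the expected change in knowledge and risk perception, and awareness is open to the same carry-over, so part of any rise in these three measures could reflect repeat interviewing.

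How large that part is cannot be said. Under random draws and a 0.2 SD learning effect, the 12-month shift lies between about 0.02 and 0.05 SD, with z below 1.96 throughout; only a heavier overlap would make a spurious result likely. The conclusion about wording and unused data rests on the text alone. Any statement of size rests on the assumptions listed in the working. The finding limits what a rise in the Aim 2 measures can be taken to mean; it does not show that such a rise, or the Aim 1 result, would be false.

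**What to change.** 1. In the Aim 2 limitations, replace the claim with one that agrees with Aim 1: some respondents may have been interviewed before, so the bias may be reduced relative to a cohort but is not avoided.
2. Report the number and share of previously surveyed respondents at 6 and 12 months, by the earlier wave they name.
3. Keep all respondents as the main analysis set. Pre-specify a sensitivity analysis restricted to first-time respondents at 6 and 12 months for the Aim 2 change tests, the Aim 2 interaction tests and the Aim 1 contrast with baseline.
4. Report the within-wave difference between previously surveyed and first-time respondents as descriptive, with a note that it combines selection and learning.

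No new data are needed. The costs are lower precision in the restricted set, and the possibility that first-time respondents at later waves are selected differently from the baseline sample. Agreement between the two analyses would be reassuring, and disagreement would call for caution; neither would identify the bias.
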